### Study population

The study population will consist of cleaners performing predominantly cleaning in day-care institutions, offices, hospitals and schools. The cleaners are employed at one of the enrolled companies in the suburban area of Copenhagen, Denmark.

Inclusion criteria at company level were more than 50 employed cleaners, possibility for the cleaners to participate in the project-activities during paid working time and location of the company in the suburban area of Copenhagen. Inclusion criteria at participant level were employment as cleaning assistant for > 20 hours per week, being between 18 and 65 years of age, and giving signed, informed consent.

Exclusion criteria for participating in the intervention are employment < 20 hours per week as a cleaning assistant, age below 18 years or above 65 years, declining to sign the informed consent, and pregnancy. Further, criteria of exclusion to specific physical tests are congestive heart failure, hospital admission for myocardial infarction or acute coronary syndrome within the last two years, hypertension (≥ 160/≥ 100 mmHg), angina pectoris, serious or chronic illness, severe trauma, frequent migraine, fever on the day of testing, and allergy to adhesive plasters for the diurnal measurements.

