### Randomization

The employees who volunteer to participate in the study and attend the baseline health check will be randomized to either a reference or an intervention group. The randomization will be performed at cluster-level for prevention of contamination between participating colleagues, Figure2. Clusters are set within strata. Each stratum is formed according to which manager the participant reports to. The clusters will be balanced on geographical work location, gender, age and seniority. Within each stratum, the clusters will be paired to minimize imbalance across several strata. Clusters will be paired according to number of participants, gender, age and seniority. Strata will be named alphabetically, and clusters will be named consecutively within each stratum. The randomization will be carried out by researchers blinded to the identity of the strata and clusters. All paired clusters assigned to the specific stratum will be drawn from an opaque, tossed bag and will be alternately allocated to either reference or intervention group, depending of the flip of a coin. Tails will decide allocation of the first of the two drawn paired clusters to the reference group and heads to the intervention group. The second of the two drawn paired clusters will be allocated to the opposite group to the first.

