### Intervention group

The intervention group will be offered supervised aerobic exercise of 60 minutes duration split into 2–3 weekly sessions during the first phase of the intervention. The weekly number of sessions will be decided within the individual company. The degree of supervision will be reduced during the second phase of the intervention, in which the participants will be encouraged to continue with the aerobic exercise themselves. The progressive reduction in supervision is to investigate the ability of the cleaners to participate and perform the aerobic exercise without external involvement.

To increase the cardiorespiratory fitness, the aerobic exercise will be aimed to be performed at an intensity of > 60 % of maximal oxygen consumption (VO_2_max) [29]. The types of aerobic exercise will be tailored to the specific worksite through a modified intervention mapping approach, Table1.

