### Data collection and study materials

Data collection will be conducted at three time points: At baseline, four and 12 months after baseline. The data collection will consist of a health check consisting of a questionnaire-based interview, physical testing of health and capacity-related measures, and objective diurnal measures of heart rate, physical activity, body position and blood pressure. At all time points, the questionnaire and the data collection will be conducted by test instructors blinded to the randomization of the participants.

The participant will get instant feedback from the physical testing in the health check, except for the venous blood sample, from a test-instructor. If some of the measured values are above the recommended levels from international and Danish health organizations [30,31], the participant will be informed and encouraged to contact a physician.

A structured interview with validated measures will be conducted. The interview will involve sociodemographic measures i.e. sex, ethnicity, country of birth, occupational group, employment status and education [32], lifestyle behaviour and health i.e. alcohol consumption, medicine use, parental history of cardiovascular disease, sleeping behaviour, level of physical activity in occupation and leisure [33], general health, modified items of the Nordic questionnaires for the analysis of musculoskeletal disorders [34], rate of perceived physical exertion [35], items from Copenhagen psychosocial Questionnaire [36], and items from the workability scale [37].

Objective physical measures of weight, percent body fat, (Tanita BC418), height (seca model 213 1721009), body mass index (BMI), waist and hip circumference (WHR) (seca 201), a venous blood sample, blood pressure (Omron M6 comfort) and level of cardiorespiratory fitness by a sub-maximal step test.

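### The cardiac, blood-pressure and serious-illness criteria bar unnamed physical tests but not the exercise itself

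*Protocol article*

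**What the plan says.** The Study population section of the protocol article gives two exclusion lists with different scopes.

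- The first governs the intervention: "Exclusion criteria for participating in the intervention are employment < 20 hours per week as a cleaning assistant", then age outside 18 to 65, and finally "declining to sign the informed consent, and pregnancy".
- The second governs testing: "criteria of exclusion to specific physical tests are congestive heart failure, hospital admission for myocardial infarction or acute coronary syndrome" in the last two years. It goes on to blood pressure of at least 160/100 mmHg, angina, serious or chronic illness, severe trauma, frequent migraine, fever on the test day and allergy to plasters.

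The Randomization section defines who is allocated: "The employees who volunteer to participate in the study and attend the baseline health check will be randomized".

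Under Intervention group: "The intervention group will be offered supervised aerobic exercise of 60 minutes duration", divided over two or three sessions a week in the first phase. On intensity, "the aerobic exercise will be aimed to be performed at an intensity of > 60 % of maximal oxygen consumption". In the second phase supervision is cut back and "the participants will be encouraged to continue with the aerobic exercise themselves".

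For values above recommended levels at the health check, Data collection and study materials says that "the participant will be informed and encouraged to contact a physician".

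**The concern.** The plan regards heart failure, a recent coronary admission, angina and markedly raised blood pressure as reason enough to keep someone out of a physical test. It does not carry the same caution over to the exercise programme, which is the study's main physical exposure. The gap comes from a scope that the article states, so it is not simply a detail left out of a condensed text.

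Participant safety is at stake. The Background describes cleaners as a group with much hypertension and cardiovascular disease, so such candidates cannot be dismissed as implausible. The second phase matters most, because participants are then expected to carry on more independently.

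**Working it through.** No figure in the plan bears on this point and no arithmetic applies. The check is to follow one hypothetical volunteer through the text: a consenting, non-pregnant cleaner aged 50 who works 30 hours a week and has angina.

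1. **Inclusion (Study population).** More than 20 hours a week, aged 18 to 65, signed consent. All are met.
2. **Exclusion from the intervention (same section).** Hours, age, consent, pregnancy. None applies. Pregnancy is a medical criterion, so this list is not purely administrative. The authors put one medical condition here and the cardiac ones elsewhere.
3. **Exclusion from tests (same section).** Angina is listed, so the volunteer is kept out of one or more tests. The section does not say which. The step test is the only exertional test described under Data collection and study materials, which makes it the likely target. Plaster allergy is tied expressly to the diurnal measurements, so the list clearly serves more than one procedure.
4. **Randomisation (Randomization).** The conditions are volunteering and attending the health check. Being fit for, or completing, the physical tests is not among them. The volunteer is randomised.
5. **Exposure (Intervention group).** If allocated to the intervention, the volunteer is offered 60 minutes a week aimed above 60 % of VO2max. Sessions are supervised at first, with less supervision later.

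The same path is open for each of the other four conditions: heart failure, a recent coronary admission, blood pressure at or above the limit, and serious or chronic illness.

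The remaining question is whether another part of the article closes the path:

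| Possible safeguard | Where | Does it bar or delay exercise? |
|---|---|---|
| Ethics approval | Study design | Does not alter the written criteria |
| Screening questionnaire | Recruitment of the study population | Described as the route for signing up; no medical exclusion attached |
| Adjustment of the exercise as it proceeds | Table 1 | No link to the cardiac or blood-pressure criteria |
| Supervision | Intervention group | Reduced in the second phase |
| Advice to contact a physician | Data collection and study materials | Advice only; exercise does not wait for the outcome |

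None of the five does.

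**The case against.** The strongest reply is that the article condenses a longer protocol, and that clearance before exercise is the kind of procedure such an article leaves out. The screening questionnaire's content is not given, and ethics approval was obtained. This has force against any claim that no clearance took place. It does not answer the point made here, because the article states what each list governs and assigns the cardiac criteria to tests alone.

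A second reply is that stricter rules for a test than for training need not be contradictory. The step test escalates from 0.2 to 0.8 steps per second and ends when the participant cannot keep up, whereas training can be adjusted and is at first supervised. This stands in part. A reader might set the test's six-minute maximum against the weekly hour and infer that the exercise is the heavier load. That compares minutes and not load, and for some people the test may be the harder bout. The reply is weakest for the second phase.

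A third reply is that hypertensive cleaners are central to the study, since lower ambulatory blood pressure is one of its two main hypotheses. This is fair. It argues for a clearance route in place of a flat exclusion, but not for having no check.

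**Conclusion.** The point holds as a gap in a stated eligibility rule and should be fixed. As written, someone barred from physical testing because of a cardiac condition, blood pressure of at least 160/100 mmHg or serious or chronic illness remains eligible for randomisation and for the exercise. The conclusion rests on reading the two lists literally and on finding no other rule in the article. That the barred test is the step test is an inference, but the conclusion does not depend on it.

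Its size cannot be stated: the article does not say what share of cleaners meets any of these criteria.

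Two stronger readings are tempting and are not supported.

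- A reader might infer that people with heart disease will in fact exercise without a medical check. The article leaves this possible but does not show it, since unreported screening may exist.
- A reader might infer that the comparison between groups will be biased because unsafe participants are withdrawn from the exercise group alone. The article describes no such withdrawal, and it plans an intention-to-treat analysis. The possibility is a reason to apply the check before allocation, but it is not a demonstrated flaw.

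**What to change.** In Study population, extend the following to participation in the exercise as well as to the tests:

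- congestive heart failure;
- admission for infarction or acute coronary syndrome within two years;
- angina;
- blood pressure of at least 160/100 mmHg;
- serious or chronic illness, where it makes exercise unsafe.

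Check them at the baseline health check, before randomisation and in the same way for everyone, so that the rule acts equally on both groups. Allow an exception where clearance to exercise is documented or, for blood pressure, where a repeat reading falls below the limit. Keep fever on the day and plaster allergy as test-only criteria. It would also help to name the tests that each remaining criterion governs.

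The cost is mainly wording. Resting blood pressure is already taken at the health check, and the test criteria must be known before testing. Slightly fewer cleaners will be eligible, including some hypertensive ones who matter for the blood-pressure hypothesis; the exception limits that loss. Some candidates will need a repeat reading or contact with a physician before they can be randomised.

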### Recruitment of the study population

Recruitment of companies took place by direct contact by phone or email of management in cleaning companies in the suburban area of Copenhagen, Denmark. If the management showed an interest in taking part in the project, a meeting was arranged by the project leader and management staff of the company. At the meeting, the aim, content and activities of the project were described and the possibility of enrolment to the study was discussed. Once collaboration was confirmed, details about the recruitment of employees were settled. All employees were invited to an information meeting where the project was described, and assignment to voluntarily participation was conducted via a screening questionnaire. Prior to the information meeting, written information about the aim, content and activities was distributed to all employees.

### Randomization

The employees who volunteer to participate in the study and attend the baseline health check will be randomized to either a reference or an intervention group. The randomization will be performed at cluster-level for prevention of contamination between participating colleagues, Figure2. Clusters are set within strata. Each stratum is formed according to which manager the participant reports to. The clusters will be balanced on geographical work location, gender, age and seniority. Within each stratum, the clusters will be paired to minimize imbalance across several strata. Clusters will be paired according to number of participants, gender, age and seniority. Strata will be named alphabetically, and clusters will be named consecutively within each stratum. The randomization will be carried out by researchers blinded to the identity of the strata and clusters. All paired clusters assigned to the specific stratum will be drawn from an opaque, tossed bag and will be alternately allocated to either reference or intervention group, depending of the flip of a coin. Tails will decide allocation of the first of the two drawn paired clusters to the reference group and heads to the intervention group. The second of the two drawn paired clusters will be allocated to the opposite group to the first.

### Development and planning of the intervention

The activities offered to the intervention group are specified and adjusted to the respective company by a modified intervention mapping approach [28]. The intervention mapping facilitates participation and consultation of all participating stakeholders (organization, management, employees, researchers, intervention- and test-instructors).

The detailed protocol for the intervention was based on three key points: 1) feasibility; it should be possible to execute the intervention at or nearby the enrolled company, during paid working time; 2) motivation; the intervention activities should apply to the participants’ preferences; 3) a standardized protocol for a scientific evaluation. According to the steps of the intervention mapping [28], the following were defined, Table1. 

**Table 1 T1:** The plan and overview of the intervention mapping procedure

**Outcomes**	**Tasks**	
Programme objectives	*Performance objective*	- decrease risk of cardiovascular disease
	*Changeable determinant*	- increase cardiorespiratory fitness
	*Target population*	- cleaners
Theoretical methods	*Literature review*	- > 60 % of VO_2_max > 60 min/week
	*Method to strategy*	- worksite-adjusted intervention
Programme design	*Strategy to plan*	- facilitating specific worksite group
	*Instruction materials*	- aerobic exercise sessions
	*Pre-test materials*	- pilot study with cleaners
	*Intervention materials*	- adjusted aerobic exercise sessions
Adoption and implementation plan	*Linkage system*	- facilitating specific worksite group
	*Adoption objectives*	- registration of conducted planned activities
		- target group participation
	*Adoption determinants*	- logistic planning of work and activities
		- collaboration between organisation and researchers
	*Implementation plan*	- activities planned in collaboration
Monitoring and evaluation plan	*Evaluation model*	- participation registration
		- on-going adjustments in aerobic exercise
	*Effect evaluation*	- increased cardiorespiratory fitness
		- decreased diurnal blood pressure
		- improve self-rated work productivity
		- reduce rate of RPE during work
		- improve metabolic cardiovascular risk factors
		- reduce the need for recovery
		- reach of target group
	*Process evaluation*	- delivering of activities
		- receipt of activities

### Reference group

The reference group receives 5 lectures of 2 hours/lecture during the one year intervention period. The lectures will concern healthy living. None of the lectures will address physical activity. Participants in the reference group will be invited to give suggestions for the proposed lectures. The lectures will be held at the enrolled company during paid working time.

### Intervention group

The intervention group will be offered supervised aerobic exercise of 60 minutes duration split into 2–3 weekly sessions during the first phase of the intervention. The weekly number of sessions will be decided within the individual company. The degree of supervision will be reduced during the second phase of the intervention, in which the participants will be encouraged to continue with the aerobic exercise themselves. The progressive reduction in supervision is to investigate the ability of the cleaners to participate and perform the aerobic exercise without external involvement.

To increase the cardiorespiratory fitness, the aerobic exercise will be aimed to be performed at an intensity of > 60 % of maximal oxygen consumption (VO_2_max) [29]. The types of aerobic exercise will be tailored to the specific worksite through a modified intervention mapping approach, Table1.

### Data collection and study materials

Data collection will be conducted at three time points: At baseline, four and 12 months after baseline. The data collection will consist of a health check consisting of a questionnaire-based interview, physical testing of health and capacity-related measures, and objective diurnal measures of heart rate, physical activity, body position and blood pressure. At all time points, the questionnaire and the data collection will be conducted by test instructors blinded to the randomization of the participants.

The participant will get instant feedback from the physical testing in the health check, except for the venous blood sample, from a test-instructor. If some of the measured values are above the recommended levels from international and Danish health organizations [30,31], the participant will be informed and encouraged to contact a physician.

A structured interview with validated measures will be conducted. The interview will involve sociodemographic measures i.e. sex, ethnicity, country of birth, occupational group, employment status and education [32], lifestyle behaviour and health i.e. alcohol consumption, medicine use, parental history of cardiovascular disease, sleeping behaviour, level of physical activity in occupation and leisure [33], general health, modified items of the Nordic questionnaires for the analysis of musculoskeletal disorders [34], rate of perceived physical exertion [35], items from Copenhagen psychosocial Questionnaire [36], and items from the workability scale [37].

Objective physical measures of weight, percent body fat, (Tanita BC418), height (seca model 213 1721009), body mass index (BMI), waist and hip circumference (WHR) (seca 201), a venous blood sample, blood pressure (Omron M6 comfort) and level of cardiorespiratory fitness by a sub-maximal step test.

Weight and percent body fat will be estimated by a Tanita BC418. Measurement will be made while the participant is wearing light clothes and no shoes. Estimated weight of clothes (1.5 kg) will be subtracted from body weight. Percent body fat will be estimated by bio-electric-impedance-analysis from electricity running from foot to foot and hand to hand [38]. Height will be measured while the participant is standing looking straight forward and wearing no shoes. Calculation of BMI by the equation of BMI = (body weight (kg)/body height (m^2^)) [30,39]. Waist and hip circumference will be measured while the participant wears light clothes and is standing looking straight forward. The waist is defined as the narrowest point between the lowest rib and the iliac crest [30,39]. The WHR is calculated by waist circumference (cm)/hip circumference (cm). A 25 ml blood sample will be drawn from the vena brachialis by a bio-analyst. Blood pressure will be measured on the left upper arm after 15 minutes of sitting at rest. Level of cardiorespiratory fitness will be estimated by a sub-maximal step test. The step test is conducted on a bench of 30 cm height for females and 35 cm for males. The step frequency is increased from 0.2 steps per second to maximal 0.8 steps per second, at the maximal 6 minutes of testing time. The step test is terminated when the participant is unable to follow the rhythm of the steps or unable to extend the knee properly.

Diurnal measurements of heart rate, physical activity, body position and ambulatory blood pressure will be conducted after each health check. Heart rate, physical activity and body position will be measured over four days and during both working and non-working days. Ambulatory blood pressure will be measured over 24 hours on a day including work. Cleaners will be instructed to write a log of working hours, sleeping and waking time and time periods spent without monitors. Cleaners will be given practical information about how to wear and treat the monitors.

The diurnal measurements of heart rate will be performed with Actiheart [40], to assess type of physical activity and body position the Actigraph GT3X + [41] will be used and for ambulatory blood pressure the Spacelabs 90217 [42].

Actiheart measures electrocardiographic raw signals with a sensitivity of 0.25 mV. Heart rate is calculated by the interbeat intervals between the R peaks in the QRS complex. Actiheart is initialised by the height, weight, gender and age of each participant. Actiheart is validated for measurement of heart rate, heart rate variability and estimation of energy expenditure in the field [43-45]. Actiheart will be mounted with ag-ag-cl pre-gelled electrodes (Ambu blue sensor VL-00-S/25) at one of the validated positions at the apex of sternum with a horizontal wire to the right at the level of the 5^th^ and 6^th^ intercostal space or at the manubrium of the sternum with a horizontal wire to the right at the level of the 2^th^ and 3^th^ intercostal space [46].

Actigraph measures accelerations in 3 dimensions with a dynamic range of ± 6 G, sampled with a precision of 12 bit. Actigraph is validated for estimation of type of physical activity in the field [47,48]. The accelerometers are initialised for recording and data downloaded using the manufacturer’s software (ActiLife version 5.5). Four Actigraphs will be mounted on the skin with adhesive tape (3 M, Hair-Set, double sided adhesive tape and Fixomull, BSN medical) at the level of T1-T2, 3 cm distal to the deltoid insertion on the dominant arm, laterally to and below the iliac crest [48] and on the right thigh at the most muscular part of the quadriceps femoris, medial to the iliac crest and the top of the patella, orientated with the x-axis pointing downwards, y-axis horizontally to the left and z-axis horizontally forward. The Actigraph signals will be sampled at 30 Hz, and processed to derive the amount of steps, type of physical activity (e.g. walking, climbing stairs, running, arms above shoulder height, bending of the spine), and body positions (e.g. standing, sitting and lying) [45].

Spacelabs measures ambulatory blood pressure by oscillometry. Spacelabs is validated for measurement of blood pressure in the field [49]. The Spacelab monitor will be mounted on the non-dominant upper arm with a tube connecting the sampler to the cuff. The sampler is mounted with elastic straps around the waist. Spacelabs will be used to monitor the ambulatory blood pressure over 24 hours, with a frequency of every 20 minutes during waking hours, and measurements every 40 minutes during sleep [50,51].

